#### **6.2.2. Visit II**

This visit will be scheduled 10 to 18 days after the first day of menstruation following the end of the second 3-month treatment course.

During the visit, the following assessments/procedures will be performed:

- Vital signs
- Gynaecological examination including breast examination
- Urine pregnancy test
- Dispense PGL4001 (2 quarterly kits for the third and fourth 3-month treatment courses)

- Study drug compliance check
- Collect subject diary and dispense the next diary
- Record Global Study Treatment Satisfaction Questionnaire
- Record UFS Quality of Life
- Record EQ-5D Quality of Life
- Record VAS for pain
- Transvaginal ultrasound of ovaries, uterine volume, total volume of the three largest myomas (identified at visit 1 in PGL09-026) and endometrium thickness
- Perform endometrium biopsy if endometrium thickness at transvaginal ultrasound >18mm or if there are any other clinical reasons to do so
- Record any new or change in concomitant medication since the previous visit or new one
- Record adverse events

Subject will be instructed to begin the third 3-month (84 days) treatment course on the first day of her next menstrual bleeding following visit II.

Subject will be instructed to begin the fourth 3-month (84 days) treatment course on the first day of the second menstruation following the end of the previous treatment course.

Subject must be instructed that once she has finished the fourth 3-month treatment course, she must call the site on the first day of her menstruation following the end of the previous treatment course to schedule the next visit III (10 to 18 days after the start of menstruation). The appointment should be in the morning if possible for blood samples. As blood lipids will also be assessed, the subject will need to have a light meal in the evening and be fasting overnight prior to the visit III.

Subjects will be instructed to bring their used and if applicable their unused blisters and diary card to the next visit III.

**If menstrual periods have not returned for 6 months during a drug free period, the subject will be asked to attend an early termination visit (see section 6.2.5). During this visit, blood samples for FSH and E2 will be assessed.**

### **6.2.3. Visit III – Post-treatment period**

This visit will be scheduled 10 to 18 days after the first day of menstruation following the end of the fourth 3-month treatment course. Subjects will need to be fasting overnight for this visit.

During the visit, the following assessments/procedures will be performed:

- Body weight

- Vital signs
- Gynaecological examination (including breast examination)
- Urine pregnancy test
- Study drug compliance check, all blisters should have been returned
- Collect subject diary
- Record Global Study Treatment Satisfaction Questionnaire
- Record UFS Quality of Life
- Record EQ-5D Quality of Life
- Record VAS for pain
- Transvaginal ultrasound of ovaries, uterine volume, total volume of the three largest myomas (identified at visit 1 in PGL09-026) and endometrium thickness
- Perform endometrium biopsy
- Record any new or change in concomitant medication since the previous visit or new one
- Record adverse events
- Blood samples for haematology, chemistry and lipids

Subject must be instructed that the next visit IV should take place 10-18 days after start of third menstruation following end of the fourth 3-month treatment courses or 3 months after last dose of the fourth 3-month treatment course (at least ten days after the last menstruation, if applicable), whatever arrives first.

#### **6.2.4. Visit IV – Follow-up visit**

Visit IV should take place 10-18 days after start of third menstruation following end of the fourth 3-month treatment course or 3 months after last dose of the fourth 3-month treatment course (at least ten days after the last menstruation, if applicable), whatever arrives first.

During the visit, the following assessments/procedures will be performed:

- Vital signs
- Gynaecological examination including breast examination
- Urine pregnancy test
- Record Global Study Treatment Satisfaction Questionnaire

- Record UFS Quality of Life
- Record EQ-5D Quality of Life
- Record VAS for pain
- Transvaginal ultrasound of ovaries, uterine volume, total volume of the three largest myomas (identified at visit 1 in PGL09-026) and endometrium thickness
- Perform endometrium biopsy, if endometrium histology differs from “benign physiologic” endometrium in the biopsy performed at visit III
- PAP smear (if no PAP smear performed in the past 12 months)
- Record any new or change in concomitant medication since the previous visit or new one
- Record adverse events
- Complete end of study page

#### **6.2.5. Early termination visit**

If the subject is withdrawn from the study at any point, she must complete an early termination visit. This visit, which includes the same assessments as visit IV, will take place 10-18 days after the beginning of menses, so that an endometrium biopsy can be taken, if applicable.

- Vital signs
- Gynaecological examination including breast examination
- Urine pregnancy test
- Record Global Study Treatment Satisfaction Questionnaire
- Record UFS Quality of Life
- Record EQ-5D Quality of Life
- Record VAS for pain
- Transvaginal ultrasound of ovaries, uterine volume, total volume of the three largest myomas (identified at visit 1 in PGL09-026) and endometrium thickness (if applicable)
- Perform endometrium biopsy, if applicable
- PAP smear (if no PAP smear performed in the past 12 months)
- Record any new or change in concomitant medication since the previous visit or new one
- Record adverse events

- Blood samples for FSH and E2 if the reason for the early termination visit is that no menstruation occurred for 6 months during a drug free period
- Study drug compliance check
- Complete end of study page, including reason for withdrawal

### **6.3. EFFICACY OBSERVATIONS AND MEASUREMENTS**

#### **6.3.1. Quality of life**

Subjects will complete one paper Global Study Treatment Satisfaction Questionnaire (see APPENDIX C) at each visit to assess their treatment satisfaction.

Subjects will complete paper UFS Quality of Life (see APPENDIX D) and EQ-5D questionnaires (see APPENDIX E) at visits II, III and IV (and Early Termination, if applicable) to determine maintained Quality of life.

There are two Baseline scores for the Quality of Life questionnaires: Baseline UFS-Qol and EQ-5D scores will be the scores recorded at visit 2 (Baseline I) of Pearl III (PGL09-026) and at visit F (Baseline II) of Pearl III extension (PGL09-027).

#### **6.3.2. Pain**

A Visual Analog Scale (VAS) (see APPENDIX F) evaluating the pain over the last month will be completed by each subject at visits II, III and IV (and Early Termination, if applicable).

Baseline pain scores will be the scores recorded at visit 2 (Baseline I) of Pearl III (PGL09-026) and at visit F (Baseline II) of Pearl III extension (PGL09-027), similar to the quality of life questionnaires.

#### **6.3.3. Myoma and uterine size**

Total volume of the three largest myoma (identified at visit 1 of PGL09-026) and uterine size will be measured using transvaginal ultrasound at visits II, III and IV. Myoma volume will be measured by measuring three dimensions of the three largest myomas. For subjects having a gap of more than 3 months between visit F of PGL09-027 and the beginning of this study, a transvaginal ultrasound will be performed at visit I.

Myoma size will not be measured if the subject has undergone uterine surgery. If it is not possible to measure the size of a myoma that was present at a previous visit, it should be clarified whether this is because of technical problems or because the myoma has disappeared or shrunk in size to a point where measurement is not possible.

There are two Baselines for myoma and uterine size: myoma and uterine size recorded at visit 1(Baseline I) of Pearl III (PGL09-026) and at visit F (Baseline II) of Pearl III extension (PGL09-027).

If possible, the ultrasound should be performed by the same assessor at each visit.

#### **6.3.4. Uterine bleeding pattern**

Subjects will record their bleeding pattern using the Pictorial Bleeding Assessment Chart (PBAC) (see APPENDIX B) for the first 8 days of the first menstruation at re-start of the first treatment course (in Pearl extension 2) in the subject diary.

The baseline for PBAC is the PBAC taken at the first menstruation (day 1-8) following visit 1 of the Pearl III (PGL09-026) study.

### **6.4. SAFETY OBSERVATIONS AND MEASUREMENTS**

Adverse event data will be collected continuously during the study as described in Section 8.

AE data will be obtained at scheduled study visits based on body weight, vital signs measurement, gynaecological and breast examination, biological laboratory assessments (haematology, chemistry, lipids, hormones FSH and E2), transvaginal ultrasound of ovaries, uterus, endometrium and myomas, endometrium biopsy and any other specific assessment (see Schedule of Study Assessments in APPENDIX A). In addition, subjects may report AEs spontaneously to investigator at any time and/or through questioning.

Complete appropriate data on all AEs experienced for the duration of the reporting period, as defined in section 8.5, will be reported on an ongoing basis in the AE pages of the eCRF.

#### **6.4.1. Body weight**

Body weight will be measured with the subject in ordinary indoor clothing and without shoes at visit III.

#### **6.4.2. Vital Signs**

Systolic and diastolic blood pressure (mmHg) and pulse rate (beats per minute (bpm)) will be measured in the supine position after resting 5 minutes at each visit.

#### **6.4.3. Gynaecological and Breast examination**

Gynaecological examinations, including breast examination, will be performed at visits I (if applicable), II, III and IV (and Early Termination, if applicable).

#### **6.4.4. Transvaginal ultrasound of ovary, uterus, endometrium and myomas**

If possible, the transvaginal ultrasound should be performed by the same operator at each visit. If possible it should be performed prior to the endometrium biopsy, if applicable.

A transvaginal ultrasound of the ovaries, uterus size, myoma size and endometrium thickness will be performed at visits II, III and IV. For subjects having a gap of more than 3 months between visit F of PGL09-027 and the beginning of this study, a transvaginal ultrasound will be performed at visit I. At these visits the size (length, height and depth) of the three largest myomas will be measured (see section 6.3.3.). The same three largest myomas identified at visit 1 in PGL09-026 should be followed-up.

#### **6.4.5. Laboratory Evaluation**

For laboratory safety examinations, blood samples will be collected by experienced staff members at visit III (See APPENDIX A). Subjects will be asked to fast overnight before blood sampling as blood lipids will also be assessed.

See APPENDIX G for the detail of laboratory parameters tested.

Blood samples will be analysed in the central clinical laboratory. Actual laboratory reference ranges will be filed at Investigator's site. All laboratory results will be assessed for clinical significance by the Investigator or one of the co-Investigators.

### **6.5. OTHER OBSERVATIONS AND MEASUREMENTS**

#### **6.5.1. Endometrial Biopsy**

The sample collection of endometrial tissue will be performed by a gynaecologist at visit III for all subjects. For the collection of the endometrium tissue sample, a Pipelle de Cornier® (see APPENDIX H) is recommended. In order to allow collection of sufficient biopsy material, the biopsy should be performed in the late proliferative or secretory phase of the menstrual cycle (i.e., at least 10 days after and ideally not later than 18 days after the start of menstruation).

Subjects for whom visit I is on a different date than visit F (Follow-up visit in study PGL09-027), an endometrial biopsy is to be performed in the following three situations:

- visit E endometrial biopsy indicated the need to perform a visit F biopsy, however visit F biopsy could not be obtained
- visit F biopsy was obtained however evaluated as "not adequate"
- for all subjects having a gap of more than 3 months between visit F of PGL09-027 and the visit I of this study.

At visit II an endometrium biopsy will be performed only if endometrium thickness measured by transvaginal ultrasound is greater than 18mm or if there is any other clinical reason to perform the assessment.

If there is a finding in the biopsy taken at visit III other than “benign physiologic” endometrium, an additional biopsy will be performed at visit IV.

These biopsies will be collected, shipped, centrally processed and reviewed by three independent pathologists, using a rating scale which they helped to develop for this purpose as part of a group of pathologists experienced in these specific endometrial changes. The rating scale is the same which was used in Pearl III (PGL09-026) and in Pearl III extension (PGL09-027).

Subjects, who discontinue the study prior to the end of the study and have been exposed to at least 4 weeks of ulipristal acetate treatment, will be asked to attend an early termination visit, which includes the same assessments as visit IV, preferably 10-18 days after the beginning of menses, if applicable, so that an endometrium biopsy can be taken and sent to the 3 independent expert pathologists.

Subjects having no return of menses for 6 months during a drug free period will be asked to attend an early termination visit including an endometrium biopsy (if not pregnant).

## **6.6. CONCOMITANT MEDICATIONS AND THERAPIES**

### **6.6.1. Permitted Medicines**

Any medications other than those excluded by the protocol, which are considered necessary for the subjects' welfare and/or which will not interfere with the study medication, may be given at the discretion of the Investigator.

The Investigator will record in the appropriate section of the eCRF all concomitant medications taken by the subject during the study from the date of signature of informed consent and for the duration of the reporting period as defined in section 8.5.

### **6.6.2. Prohibited Medicines**

Medications listed in exclusion criteria (5.2.2) will be prohibited during the entire study.

However, when a prohibited medication or treatment is necessary for the subject's wellbeing, the sponsor must be notified and possible alternatives are to be discussed before administration of the prohibited medication or treatment whenever possible.

### **6.6.3. Non-Drug Therapies**

Current non-drug therapies for uterine myoma include the following surgical procedures: hysterectomy, myomectomy and uterine artery embolization and are prohibited during the course of the study and will lead to subject withdrawal.

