### **3.3. EXPLORATORY ENDPOINTS:**

- Frequency of PAEC observed in the endometrial biopsy, on day10-18 after the first menstruation following the last treatment course with ulipristal acetate.
- Proportion of subjects having surgery or any invasive procedure for myoma treatment at any time during the study (type of surgery/ procedure performed).

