### 6.7.2. Subject Withdrawal from Study

Subjects will be informed that they have the right to withdraw from the study at any time, without prejudice to their medical care, and that they are not obliged to state the reason(s). Any withdrawal must be fully documented in the End of Study page of the CRF and should be followed up by the Investigator.

The Investigator may withdraw a subject at any time if this is considered to be in the subject's best interest.

During the course of a study, the subject may be withdrawn for the following reasons:

- **Lack of efficacy:** Investigator judgment only. If subject's opinion only, check Subject Request. Explain in the eComment section of the eCRF End of Study page.
- **Adverse event:** Includes clinically significant new or worsening existing condition as judged by the investigator. Documented in the AE form.
- **Subject request:** Consent withdrawal, subject moved, schedule conflicts, etc. Specify the reason in the eComment section of the eCRF End of Study page.
- **Protocol violation:** Major protocol violation which would confound interpretation of the results. Specify the protocol violation in the eComment section of the CRF End of Study page.
- **Lost to follow-up:** Two documented phone calls and a registered letter requesting acknowledgement of receipt without response. Document in the eComment section of the CRF End of Study page.
- **Pregnancy:** **Study drug must be immediately discontinued.** Complete the Pregnancy Surveillance Form (see section 8.6 of protocol).
- **Missing return of menstruation:** Subjects having no return of menses for 6 months during a drug free period will be withdrawn.

- **Other:** Specify in the eComments section on the eCRF End of Study page. This reason should only be used if the reason for discontinuation is not better accounted for by another category.

Subjects who undergo any type of surgery or intervention which would interfere with study endpoints (i.e. hysterectomy, myomectomy, uterine artery embolization (UAE), etc.) will be discontinued from the study.

Subjects, who discontinue after at least four weeks of treatment with ulipristal acetate, will be asked to undergo the same assessments as those planned during visit IV, plus an endometrium biopsy.

Subjects, who discontinue prior to four weeks of treatment with ulipristal acetate, will be asked to attend a follow-up visit, which will include the same assessments as visit IV, without an endometrium biopsy.

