## 8.3. SERIOUS ADVERSE EVENTS

### 8.3.1. Definitions

A **Serious Adverse Event** (SAE) is defined as any untoward medical occurrence or effect that at any dose:

- **results in death,**  
i.e. the AE causes or contributes to the death.
- **is life-threatening,**  
i.e. the AE places the subject at immediate risk of death; it does not refer to AE which hypothetically might have caused death if it were more severe.
- **requires inpatient hospitalization or prolongation of existing hospitalization,**  
i.e. the AE requires at least an overnight admission or prolongs a hospitalisation beyond the expected length of stay. Hospital admissions for surgery planned before study entry, for social reasons, for any elective surgery (i.e. plastic surgery) or for normal disease management (including treatment adjustment) are NOT to be considered as SAE according to this criterion (i.e. if the protocol or the standard management of the disease under study requires planned hospitalisation).  
  
Subjects entering this study will most likely be eligible and may decide to undergo one of the following surgical interventions: i.e. hysterectomy or myomectomy. Scheduled hospitalisations related to these procedures will therefore **NOT** be considered a criterion of seriousness.
- **results in persistent or significant disability / incapacity,**

i.e. the AE resulted in a substantial disruption of the subject's ability to conduct normal activities.

- **is a congenital anomaly / birth defect,**

i.e. an adverse outcome in a child or foetus of a subject exposed to the Investigational Medicinal Product before conception or during pregnancy.

- **is an important medical event, i.e. is medically significant**

Medical and scientific judgment should be exercised in deciding whether an adverse event is serious in other situation. Important medical events that may not be immediately life-threatening or result in death or hospitalisation but may jeopardise the patient or may require intervention to prevent one of the other outcomes listed in the definition above should also be considered serious. Examples of such events are intensive treatment in an emergency room, or at home for allergic bronchospasm, blood dyscrasias or convulsions that do not result in hospitalisation, or development of drug dependency or drug abuse.

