### **9.4. POPULATION FOR ANALYSIS**

The Full Analysis Set (FAS) is defined as all subjects who are enrolled into PGL11-024 and who receive at least one dose of PGL4001. Both safety and efficacy will be evaluated on the FAS. Sub-group analyses may be conducted based on subjects who have fully completed 2 treatment cycles (attended visit II) or all 4 treatment cycles (attended visit III) of PGL11-024.

The Completer's Set is defined as all subjects who complete all four cycles of treatment in PGL11-024, who do not have surgery performed up to visit III and who do not withdraw prior to study completion (defined as attending visit IV). If applicable, two summaries of visit IV will be produced for the Completer's Population. One will include subjects that had surgery performed between visit III and visit IV, and the other will exclude those subjects in the Completer's Population that had surgery performed between visit III and visit IV.

All subjects who have had at least one visit I assessment conducted but who have not subsequently received open-label PGL4001 medication in PGL11-024 at least once will be included in the not treated population.

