**9.5.5. Exploratory Analysis**

All exploratory endpoints will be summarised by descriptive statistics at each visit for the FAS and Completers Set.

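### The surgery proportion is to be summarised in a Completer's Set that excludes operated women, and the FAS figure misses surgery after the early termination visit

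*Protocol*

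**What the plan says.** Protocol 3.3 lists as an exploratory endpoint: "Proportion of subjects having surgery or any invasive procedure for myoma treatment at any time during the study". Section 6.6.3 says that hysterectomy, myomectomy and uterine artery embolization "are prohibited during the course of the study and will lead to subject withdrawal". Section 6.7.2 repeats the rule: "Subjects who undergo any type of surgery or intervention which would interfere with study endpoints" will be discontinued. The event is expected, since 8.3.1 states: "Subjects entering this study will most likely be eligible and may decide to undergo one of the following surgical interventions", naming hysterectomy and myomectomy.

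On what is recorded at exit, 6.2.5 says: "If the subject is withdrawn from the study at any point, she must complete an early termination visit". Section 6.7.2 adds: "Any withdrawal must be fully documented in the End of Study page of the CRF and should be followed up by the Investigator".

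On analysis, 9.4 defines the FAS as all enrolled women with at least one dose. It limits the Completer's Set to women who finish all four cycles, "who do not have surgery performed up to visit III and who do not withdraw prior to study completion", completion meaning attendance at Visit IV. It then provides for two Visit IV summaries in that set, one with and one without women operated on between Visits III and IV. Section 9.5.5 states: "All exploratory endpoints will be summarised by descriptive statistics at each visit for the FAS and Completers Set".

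**The concern.** The same event is an endpoint, a prohibited act and a reason to leave the study. That raises two questions: whether each planned summary can show the event at all, and whether an operation is still recorded once the woman has left.

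In the Completer's Set, the selection rule removes the outcome being counted. A table of this endpoint in that set would print a figure near zero that reflects only the definition, and in an uncontrolled study it could be read as evidence about surgery on treatment. In the FAS, the risk is an undercount of operations performed after exit. Any such error goes in one direction, towards fewer operations.

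**Working it through.** The protocol gives no surgery rate, dropout rate, power or computed sample size, so there is no stated figure to reproduce. The check compares the sections and adds illustrations whose inputs are labelled as assumed.

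**1. Completer's Set up to Visit III.** Membership requires no surgery up to Visit III (9.4). The numerator for surgery up to Visit III is therefore 0, and the proportion is 0/n = 0% for any true rate.

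**2. Completer's Set between Visits III and IV.** Three statements meet here:
- 6.6.3 and 6.7.2: a woman who has such surgery is withdrawn.
- 9.4: a woman who withdraws before attending Visit IV is not in the set.
- 9.4: one Visit IV summary of the set includes women operated on between Visits III and IV.

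If the first two are applied, the third describes women who cannot be in the set, and the proportion is 0% throughout. If such women are kept, the window is short. Assume 42 to 84 drug-free days between courses, Visit III 42 days and Visit IV 90 days after the last dose, and a constant hazard. The window's share of the period is then f = (90 − 42)/(4×84 + 3×42 + 90) = 48/552 = 0.087, down to 48/(4×84 + 3×84 + 90) = 48/678 = 0.071. With assumed surgery risk s over the whole period, the proportion is 1 − (1 − s)^f:
- s = 5%, f = 0.071: 0.4%
- s = 20%, f = 0.087: 1.9%

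Either way the figure says almost nothing about surgery over the study.

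**3. FAS, size of one missed operation.** With 70 to 90 women (9.2): 1/90 = 1.1 and 1/70 = 1.4 percentage points.

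**4. FAS, effect of exits for other reasons.** Assume constant competing hazards, with surgery risk s and non-surgical exit risk d over the study, L = −ln(1 − s) and D = −ln(1 − d). Surgery that ends participation is counted; surgery after a non-surgical exit is not. The observed proportion is L/(L + D) × (1 − exp(−(L + D))).

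- d = 0, s = 10%: observed 10.0%. Surgery-triggered withdrawal alone causes no loss.
- d = 20%, s = 10%: L = 0.105, D = 0.223; observed = 0.105/0.328 × (1 − exp(−0.328)) = 9.0%. The risk over the planned period is 10.0% if the surgery hazard is unchanged after exit, and 11.8% if it triples.
- In women: 6.3 counted against 7.0 or 8.3 of 70; 8.1 against 9.0 or 10.7 of 90.
- For assumed s = 5–20% and d = 10–30%, the relative shortfall is about 5–16% (hazard unchanged) or 12–35% (tripled).

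**5. Is surgery after exit sought?** The visit lists in 6.2 and the schedule in Appendix A contain no item asking about myoma surgery, and none schedules a contact after the early termination visit. The withdrawal reasons in 6.7.2 have no category for myoma surgery, performed or planned. Scheduled admission for hysterectomy or myomectomy is not a seriousness criterion (8.3.1). After the end of the study, 8.5 asks only for related serious events. The follow-up of withdrawals required by 6.7.2 has no stated content or timing.

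**The case against.** A reader might infer that nothing is collected once a woman leaves, and that the surgery proportion is therefore driven towards zero in every analysis. The protocol does not support this. The early termination visit is mandatory, the withdrawal must be documented on the End of Study page, and the investigator is to follow it up. Several withdrawal reasons require a free-text explanation, where planned surgery could be noted, and 8.3.3 shows that the eCRF has a non-drug therapy page. In the FAS, the operation that ends participation is itself the counted event.

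A reader might also suppose that sites will complete the exit visit first and let the woman be operated on afterwards, so that surgery disappears through the order of paperwork. That is conjecture. The written order in 6.6.3 and 6.7.2 is surgery, then withdrawal, and 6.3.3 foresees assessments after uterine surgery. The protocol gives no basis for estimating how often the reverse order would occur.

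Nor are all operations invisible to safety reporting: 8.1.5 makes acute uterine bleeding that needs immediate surgery an event of special interest. Section 1.6 mentions women who decline or delay surgery, but its stated main objective does not include avoiding surgery.

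Finally, the endpoint refers to events during the study, so a count confined to participation may be what was meant, and the FAS figure is reported beside the Completer's figure. These objections hold against the broader readings. They do not rescue the Completer's Set figure, resolve the conflict over Visits III to IV, or supply a routine check for surgery after the early termination visit.

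**Conclusion.** The point holds in three parts.

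- **Completer's Set:** the planned surgery proportion is 0% up to Visit III by construction. This needs no numerical assumption, only that surgery in 9.4 covers the procedures that the endpoint counts; a procedure that leads to withdrawal is excluded in any case.
- **Contradiction:** the planned summary of women operated on between Visits III and IV conflicts with the withdrawal rule in 6.6.3 and 6.7.2 combined with the set's own definition. The passages must be reconciled.
- **FAS:** the proportion counts surgery that causes withdrawal but can only understate surgery over the planned period, because operations after the early termination visit are not systematically sought, whether planned at exit or following exit for another reason. The size is unknown. It is 1.1 to 1.4 points per missed operation; the 5–35% relative range is an illustration under assumed rates and not an estimate for this trial.

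Severity is minor. The endpoint is exploratory, the analysis is descriptive (9.1), and no primary or secondary endpoint depends on it.

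**What to change.** 1. In 9.5.5, report the surgery endpoint in the FAS only and remove it from the Completer's Set summaries.
2. Reconcile the Visit III to IV provision in 9.4 with 6.6.3, 6.7.2 and the set's own definition.
3. On the End of Study page, record myoma surgery as performed or planned, with type and date.
4. Make one telephone contact, at the expected Visit IV date, with withdrawn women who agree, and ask about any myoma surgery or procedure since exit.
5. Report on-study, planned and post-exit surgery separately, so that the count during participation stays visible.

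The cost is a wording amendment, a few eCRF fields and one call per withdrawn woman who agrees. The downside for the sponsor is that the proportion may look less favourable.
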